#### Ecological Momentary Assessment

EMAs were used to assess specific food parenting practices used during shared eating occasions, as well as to identify momentary predictors of within- and between-day variability in use of specific food parenting practices.

The EMA protocol included 2 distinct types of assessments. the first was event-contingent assessments; for these, caregivers were asked to complete an EMA survey after every eating occasion during which they were present with the enrolled child. Event-contingent assessments were initiated by caregivers after each shared eating occasion (eg, meals or snacks); caregivers simply used their phone to click on a study-provided link. Event-contingent assessments included questions on food parenting practices and the child’s food intake during that specific eating occasion. On average, participants took 4.41 (SD 6.35) minutes and a median of 2.77 minutes (IQR 1.90-4.32) to complete each event prompt. The second was signal-contingent assessments, for which caregivers were texted to complete a survey at random intervals situated within 4 time blocks throughout the day (eg, 7 AM-10 AM) to capture momentary variables of interest. Signal-contingent prompts were timed to expire after 1 hour of receipt of the text prompt. On average, participants took 1.74 (SD 2.71) minutes and a median of 1.22 (IQR 0.85-1.82) minutes to complete each signal prompt.

Caregivers were asked to complete 8 days of EMA data collection. A day was considered to be complete if they engaged in 2 event-contingent and 2 signal-contingent assessments; if a parent failed to complete adequate prompts on a specific day, they were given an additional day to complete the required prompts. At baseline, on average, it took parents 9.667 (SD 3.63 days; median 9.0, IQR 8-10) days to achieve 8 complete days. To minimize potential confounding effects of weekly rhythms (eg, weekday vs weekend variations in behavior, mood, or context), all participants began data collection on the same day of the week. This approach, which followed recommendations in the extant EMA literature [47-50], ensures that each participant’s data collection period spanned identical calendar days.

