From these responses, 10 individual food categories were created, including fruit, vegetable, whole grain, refined grain, dairy, meat protein, plant protein, sugary drinks, baked goods, and candy. A modified version of the Healthfulness of the Meal Index [29], which was adapted from the Healthy Eating Index (HEI) categories [52], was also calculated. In alignment with prior research, the Healthfulness of the Meal Index was scored using an eaten or not eaten format. For example, an eating occasion received 1 point for the child consuming each of the following foods (fruit, vegetable, whole grain, dairy, meat protein, and plant protein) and 1 point for not eating each of the following foods (refined grains, sugary drinks, baked goods, and candy). Points were then summed with a range of 0 to 10 for each eating occasion. A similar Healthfulness of the Meal Index has been used within studies using EMA protocols to conduct research within similarly diverse populations of children [53]. This measure of eating occasion–level dietary quality provided direct correspondence between food parenting practices used at each eating occasion and types of foods eaten or overall healthfulness of the foods eaten, at the same, or subsequent eating occasions, allowing for an understanding of within-meal, and within-day associations between food parenting practices and dietary quality (refer to hypothesis 3 below in the Results Section).

Momentary predictors were assessed using a combination of items developed and pilot-tested as a part of the Kids EAT! study [15,20], as well as items developed or modified for use within an EMA protocol by others. Parents reported on their current mood [27] and stress level [22], as well as their child’s current mood [28], using tools validated for use within a similar population and within an EMA protocol. Finally, additional momentary factors were assessed by asking parents to report on their experience of 12 specific factors identified within previous qualitative research as salient predictors of food parenting practices [14]. For example, parents responded to the following statement regarding how they had felt since the last assessment: “Busy with a number of work or household activities” (responses were evaluated on a 5-point Likert scale, ranging from 1=very slightly or not at all to 5=extremely).

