### Statistical Analysis Plan

#### Overview

R (R Foundation for Statistical Computing) will be used for data cleaning and main analyses. Distributions of key outcome variables will be assessed and transformed if necessary. Unless otherwise specified, hypothesis tests will be conducted using a 2-sided α level of .05.

EMA responses will be aggregated to derive scores for each of the 4 food parenting practice domains during each data collection period. Given the unequal number of questions related to each domain, 2 versions of domain scores will be created by computing (1) the number of items endorsed in each domain and (2) the proportion of items endorsed in each domain. Domain scores will be calculated for responses given at each event prompt (typically 2-8 per day over each 8-day data collection period).

Food parenting practice domain scores will be aggregated and compared visually and statistically at the event level (eg, breakfast, lunch, snack, and dinner) and by time period (eg, 9 AM to noon, 3 PM-5 PM, and 5 PM-9 PM). In addition, for each data collection period, we will fit linear mixed models for each domain of the form (M1) *D_ij_ = β_0_ + β_1_Z_ij_ + β_2_X_i_ + b_i_ + ε_ij_*, where *D_ij_* is the domain score for person *i* at event prompt *j*, *Z_ij_* is the event characteristic of interest (meal or time period indicator), *X_i_* is a set of baseline characteristics for person *i*, *b_i_* is a person-specific random effect, and *ε_ij_* is the residual. Longitudinal response patterns in domain scores will be visualized and qualitatively compared. We will calculate each individual’s SD, IQR, and entropy of domain scores across their longitudinal observations. How between-day fluctuations in food parenting differ across individuals will be quantified using longitudinal mixed models, similar to those described above, with the event characteristics *Z_ij_* representing between-day factors such as day of the week. The SD, IQR, and entropy of residuals from these models will also be summarized to characterize between-day fluctuations.

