To examine the longitudinal impact of within- and between-day fluctuations in food parenting practices on child dietary intake, we will fit regression models for the outcome of child HEI measured from 24-hour dietary recall at time points T2 to T4. The main predictors of interest will be the individual-level summary measures of the 4 food parenting practice domains derived above. Our primary models will include the subgroup indicators classifying parents according to food parenting practice patterns, but we will also consider models that use average domain scores as well as consistency and endurance metrics. We will fit separate linear regressions for each data collection period, as well as longitudinal models that incorporate data across the time points T2 to T4. For period-specific models, we will include cluster indicators as well as consistency *z* scores that reflect the degree of within- and between-day fluctuations in food parenting practices during that period, along with relevant adjustment covariates. For longitudinal models, we will also include endurance *z* scores that reflect whether food parenting practices are maintained across data collection periods.

To identify momentary predictors of within- and- between-day fluctuations in the use of food parenting practices across time and context, we will combine the signal and event EMA survey data to understand how momentary factors (eg, mood, stress, and time constraints) affect food parenting practices. The main statistical approach will be to fit longitudinal linear mixed models of the form: (M2) *D_ij_* = *β_0_* + *β_1_W_ij_* + *β_2_X_i_* + *b_i_* + *ε_ij_*. Here, *W_ij_* represents a *vector* of momentary predictors, which will be derived by summarizing signal surveys within fixed time windows before the event *j*. Initially, we will define 

, with the superscript in parentheses indicating the number of hours before the event covered by that variable. For instance, 

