 could reflect the average level of stress reported from signal surveys responded to in the 3 hours preceding the given event survey. We will fit separate models for each domain score during each data collection period; to increase power, we will also fit combined models that incorporate responses across multiple data collection periods. Single-predictor models (involving 1 type of momentary predictor, eg, stress) as well as multipredictor models will be considered. Time windows will be adjusted based on the observed response patterns of data, and if the momentary predictor data are overly sparse, multiple imputation will be used to fill in missing *W*values. In exploratory analyses, we will investigate whether momentary predictors interact with each other or with fixed and summarized individual characteristics (ie, consistency and endurance *z* scores) to impact food parenting practices. This will allow us to explore whether the strength of associations between momentary predictors and food parenting practices varies based on individuals’ levels of volatility in these practices.

Some participants may respond sporadically to event prompts, resulting in gaps between event prompt responses, which make it difficult to assess longitudinal patterns. We will begin by characterizing missing data patterns by participant and temporal factors, including the end-of-day prompts asking participants to indicate why they did not respond to prompts on a given day. Then, we will define and analyze a subset of “regularly responding” individuals for which there is sufficient data to characterize between-day fluctuations in food parenting practices, for example, a subset of individuals who have at most 2 days of event prompt nonresponse during their data collection period. To explore overall patterns and associations with non-EMA outcomes, we will augment this regularly responding set with data from individuals with more sporadic response patterns but who, based on their responses to end-of-day prompts, more plausibly have responses missing at random (eg, reported “forgot” rather than “too stressed”).

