## Results

### Overview

Recruitment and data collection began in October 2023. At the time of this protocol paper’s submission, data collection is still in progress and is expected to continue through November 2026. A racially and ethnically diverse cohort was successfully enrolled, with 28.3% (72/254) of enrolled participants identifying as White and 71.7% (182/254) identifying as Black, Indigenous, or people of color. Refer to Table 2 for detailed information on the characteristics of the Preschool Plates baseline sample.

Hypotheses

This study hypothesized the following:

Use of food parenting practices will vary within- and between-days; unique patterns will emerge across time (eg, time of day and day of week) and context (eg, location and type of eating occasion).Distinct patterns in food parenting approaches will emerge; distinct pattern features will include mean levels of engagement in specific food parenting practices (by domain), as well as consistency in approach across day-, week-, and 6-month intervals, and endurance (or lack thereof) of patterns across time.Healthful eating occasion–level dietary quality (ie, Healthfulness of Meal Index assessed via EMA) will be positively associated with supportive feeding practices (eg, structure and autonomy support) and inversely associated with unsupportive practices (eg, coercive control and indulgent).Consistent and enduring use of supportive feeding practices will be associated with a more healthful overall diet quality (ie, HEI assessed via 24-hour dietary recalls) cross-sectionally and at 2-year follow-up, as compared to inconsistent or short-lived use of supportive practices and consistent and enduring use of unsupportive practices.We expect to identify numerous momentary predictors of significance (eg, mood, stress, child behavior, and time constraints). Parents will shift within the day from supportive feeding practices toward unsupportive feeding practices in response to momentary predictors (eg, high stress, low mood, or limited time).

**Table 2 table2:** Characteristics of the Preschool Plates baseline sample (N=254).

Characteristics		Values
Child age (y), mean (SD)		3.48 (0.59)

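### Model M2: the only worked look-back window ends at the post-meal event survey, so stress or mood reported during or after a meal can count as a predictor of practices at that meal

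*Protocol article*

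**What the plan says.** The Overview of the Statistical Analysis Plan in the protocol article defines model M2 with a vector of momentary predictors, `W_ij`, "which will be derived by summarizing signal surveys within fixed time windows before the event" j. The worked illustration is that one such variable "could reflect the average level of stress reported from signal surveys responded to in the 3 hours preceding the given event survey". The same section ties the outcome to the survey: "Domain scores will be calculated for responses given at each event prompt", with j indexing the event prompt in model M1. Windows may later be changed in the light of response patterns, and sparse predictor values may be imputed.

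The section Ecological Momentary Assessment gives the timing of the two survey types.
- Event surveys: "caregivers were asked to complete an EMA survey after every eating occasion during which they were present with the enrolled child", and "Event-contingent assessments were initiated by caregivers after each shared eating occasion".
- Signal surveys: "caregivers were texted to complete a survey at random intervals situated within 4 time blocks throughout the day". They expire 1 hour after the text arrives. They record current mood and stress, and for 12 further factors the example item is introduced this way: "parents responded to the following statement regarding how they had felt since the last assessment".

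The fifth hypothesis, in the Results, is directional: "Parents will shift within the day from supportive feeding practices toward unsupportive feeding practices in response to momentary predictors".

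**The concern.** M2 is meant to show that a momentary state leads to a feeding practice, so the state must be reported before the practice occurs. A window that closes at the event survey does not secure this, because the practices are already over by then. Suppose a difficult meal includes pressure to eat and leaves the parent stressed, and a signal is answered before the event survey is opened. That stress is then coded as preceding the pressure. The resulting association has the sign that the fifth hypothesis predicts.

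Nothing else in M2 removes the problem. The person-level random effect and the baseline covariates act between persons, whereas this is a question of timing within a single event. The planned window adjustment follows response patterns, not meal times. Temporal order is a main reason for using momentary assessment, and the Conclusions say the findings will guide a real-time intervention.

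**Working it through.** The plan gives no figure for this point, so the first step is textual and the rest is illustrative.

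**1. Order of events.** The text fixes this sequence: the meal takes place; the caregiver opens the event survey afterwards; the 3-hour window in the example runs back from that survey. Signals arrive at random within blocks and can be answered up to an hour after the text. An answer can therefore fall during the meal or between meal and survey, and it would lie inside the window. A current-state item answered then describes a state during or after the meal. An item that looks back to the previous assessment can also cover the meal.

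**2. Share of the window affected.** Let L be the minutes from the point where the window ought to close to the event survey. Counted from the end of the meal, L gives the post-meal share. Counted from the start of eating, it also includes the meal's own length. With signals evenly spread in time, share = L/180 for a 3-hour window. L is an assumption.

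| L (min) | L/180 | Share |
|---|---|---|
| 0 | 0/180 | 0% |
| 6 | 6/180 | 3% |
| 15 | 15/180 | 8% |
| 30 | 30/180 | 17% |
| 60 | 60/180 | 33% |

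A simulation with one signal in each of four 3-hour blocks, 70% response and answers within the hour gave the same shares.

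**3. What that could do to M2 (illustration only).** Assume no true forward effect, and a reverse effect of 0.3 SD of stress per SD of practice score. The spurious slope is then roughly 0.3 × share: 0.3 × 0.08 = 0.02 at 15 minutes (simulated 0.025), 0.3 × 0.17 = 0.05 at 30 minutes (simulated 0.05) and 0.3 × 0.33 = 0.10 at 60 minutes (simulated 0.10). When the window closes at the meal, the simulated slope is about 0.

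A second simulation used 200 parents, 8 or 16 events each, person-centred regression and a reverse correlation of 0.1 to 0.2. The false-positive rate at .05 stayed close to nominal, roughly 5–8%, when 3–5% of signals were contaminated. It was roughly 15–79% when 25% were contaminated, which corresponds to L = 0.25 × 180 = 45 minutes. The width of that range shows how far the result depends on assumed values.

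**4. What a fixed lag costs.** Under the same signal assumptions, removing the last 60 minutes of a 3-hour window lowers the share of events with any signal from about 57% to 39%. Moving both ends back by 60 minutes keeps about 52%. With event surveys spread evenly from 10:00 to 18:00, a rerun gave 62%, 44% and 60%. In both cases, moving the window loses far less than truncating it.

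**The case against.** The strongest reply is that an example is being treated as a rule. The example is worded as a possibility, and the initial definition is provisional. The general definition speaks of windows before the event, and the same section elsewhere glosses event level as breakfast, lunch, snack and dinner, that is, the eating occasion. This stands in part: the text is ambiguous, and a reader should not infer that the analysis is firmly committed to the survey as the end point. But j indexes the event prompt and the only concrete example names the survey, so the wording needs settling.

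A second reply is that the event-survey time limit and the recording of meal times belong to the full protocol or the SAP. That stands, and their absence from the article is not part of this point. What is at issue is the anchor that the article does state.

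Third, surveys may be completed promptly, and the article asks for them after each occasion. If so, the effect is small. A reader might infer from step 3 that Aim 3 is likely to yield false positives. The documents do not support that: the delay, the contaminated share and the reverse correlation are all assumed, and short delays give nearly nominal error.

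Fourth, the Power Analysis section calls the goal descriptive, with no primary end point. This lowers the stakes, but the fifth hypothesis still states a response to predictors.

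**Conclusion.** The point holds as one of wording with a possible bias behind it. Followed as illustrated, M2 can take states reported during or after a meal as predictors of practices at that meal, and any resulting bias can run in the hypothesised direction. Its size cannot be fixed from the article. It is negligible if surveys follow within minutes of the meal and material if they commonly come half an hour or more later. The shares in step 2 rest on even signal spacing and an assumed delay. The slopes and error rates also rest on an assumed reverse effect. This is a cheap improvement, not a demonstrated failure of Aim 3.

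**What to change.** State that each look-back window in M2 ends at the start of the eating occasion, and exclude signals answered after that time. Items that look back to the previous assessment then need no separate rule, because an answer given before eating begins cannot cover that meal.

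If eating time is not recorded:
- Move the whole window, start and end, back by a fixed lag before the event-survey time stamp. Do not just cut off its last part.
- Report a second lag as a sensitivity analysis.
- Drop look-back items whose recall period may include the meal.

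A negative-control model with the first signal after the event in place of the predictor is optional.

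The change affects analysis wording and code only, and data collection is expected to run through November 2026. The cost is that some events lose their only signal or their most proximal one, so precision falls. A fixed lag also discards some truly pre-meal signals when surveys are prompt.

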### Data Collection Procedures

#### Overview

During their initial enrollment call, participants were briefed on data collection procedures, engaged in the informed consent process, and were scheduled for the in-person baseline visit.

At the baseline visit, participants received additional details on measurements and the data collection schedule and were trained on protocols for surveys, EMA, and 24-hour dietary recalls. Parents completed the baseline survey at this visit. Finally, height and weight measurements for the child participant were completed at this time. In total, Preschool Plates includes 4 data collection sessions over 2 years: baseline (T1), 6 months (T2), 12 months (T3), and 24 months (T4). T1, T3, and T4 include in-person data collection at the University of Minnesota; T2 includes only remote data collection activities.

At each time point, participants completed a survey to assess usual use of food parenting practices as well as additional parental, household, and environmental factors of interest. They also completed three 24-hour dietary recalls, reporting daily dietary intake on behalf of their child, to assess overall quality of diet and participated in 8 days of EMAs. Children’s height and weight were measured by trained study staff at T1, T3, and T4.

All participant-facing study materials were available in English and Spanish. Materials were professionally translated and then further reviewed by bilingual study staff. Bilingual study staff were also employed to engage with participants who were Spanish speaking. Data collection methods and measures for study variables of interest are presented below and summarized in Table 1.

**Table 1 table1:** Constructs of interest, study measures, and methods.

Measurement methods and constructs				Description of measure

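### If the printed momentary model M2 is pooled over T1-T4 unchanged, wave-to-wave co-movement can pass for a momentary effect and the test can exceed 5%

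*Protocol article*

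**What the plan says.** In the Statistical Analysis Plan, Overview, the analysis of momentary predictors is introduced with "The main statistical approach will be to fit longitudinal linear mixed models of the form" M2: D_ij = β0 + β1W_ij + β2X_i + b_i + ε_ij. The symbols are defined under M1: X_i "is a set of baseline characteristics for person" i, and b_i "is a person-specific random effect, and" ε_ij is the residual. There is no index for data collection period.

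On use of the model, the article says "We will fit separate models for each domain score during each data collection period", and adds that "to increase power, we will also fit combined models that incorporate responses across multiple data collection periods". It prints no equation for the combined models and neither adds nor excludes a period term. The design has "4 data collection sessions over 2 years: baseline (T1), 6 months (T2), 12 months (T3), and 24 months (T4"). Unless otherwise specified, "hypothesis tests will be conducted using a 2-sided α level of .05". Hypothesis 2 (Results, Hypotheses) anticipates that a parent's approach may or may not stay the same over 6-month intervals.

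**The concern.** Each wave is a short burst of reports, separated from the next by 6 or 12 months. If a parent's practice level moves between waves, all of that parent's reports in one wave share a deviation. With one two-year intercept per parent and only baseline covariates, nothing in M2 can absorb it, so it goes into an error term treated as independent. If the predictor (stress, mood, time pressure) also has wave-specific levels, β1 picks up slow co-movement between waves and its standard error is too small. Separately, if practice and predictor both drift across the cohort as the children age, β1 is biased, and a larger sample makes rejection more likely. Neither effect needs parents to differ in slope.

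The combined models are the ones added for power. Hypothesis 5 expects many significant momentary predictors, and this error would favour that result.

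**Working it through.** **The plan's own figures.** Nominal α is 0.05, two-sided. The Power Analysis counts 200 families × 4 responses × 8 days = 6400 records, which reproduces and is one period; four periods would give 25,600. The stated detectable momentary effect of 0.14 items implies a standard error of 0.14/(1.96 + 0.84) = 0.050. It comes from a simulation whose variance parameters are not printed, so it can be neither confirmed nor refuted.

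**Inputs.** N = 200 parents and P = 4 waves. Records per wave m = 32 (Power Analysis, counting event or signal responses) or m = 16 (8 days × the 2 event reports that make a complete day, from Ecological Momentary Assessment). Not given, so assumed: ρ_D and ρ_W, the shares of within-parent variance in practice and predictor that lie between waves.

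**Formula for parent-specific change, no true effect.** Let n = mP and λ = 1 + (m−1)ρ. The ratio of true to model-based variance of β1 is

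V = (n−1)·[(P−1)λ_Dλ_W + P(m−1)(1−ρ_D)(1−ρ_W)] / (T_D·T_W), with T = (P−1)λ + P(m−1)(1−ρ).

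Actual α = 2[1 − Φ(1.96/√V)].

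Example, ρ_D = ρ_W = 0.2 and m = 32: λ = 7.2; bracket = 3(51.84) + 124(0.64) = 234.88; T = 21.6 + 99.2 = 120.8; V = 127 × 234.88/120.8² = 2.044; α = 17.0%.

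| ρ_D / ρ_W | m = 16 | m = 32 | simulated, m = 32 (1000 runs) |
|---|---|---|---|
| either = 0 | 5.0% | 5.0% | 4.4-5.2% |
| 0.05 / 0.05 | 5.3% | 5.7% | 6.0% |
| 0.1 / 0.1 | 6.4% | 7.9% | 6.2% |
| 0.2 / 0.1 | 8.0% | 11.1% | 10.8% |
| 0.2 / 0.2 | 11.1% | 17.0% | 16.7% |

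**The same in shares of total variance.** Assume parent-level shares of 0.30 (practice) and 0.40 (predictor), so that total-variance shares convert by dividing by 0.70 and 0.60.

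| Total shares (practice, predictor) | ρ_D / ρ_W | formula, m = 16 | formula, m = 32 |
|---|---|---|---|
| 5%, 10% | 0.071 / 0.167 | 6.7% | 8.5% |
| 10%, 20% | 0.143 / 0.333 | 12.4% | 19.3% |
| 15%, 20% | 0.214 / 0.333 | 16.0% | 25.3% |

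A random-intercept simulation of 2000 runs per setting gave 6.8%, 11.9% and 15.5% at m = 16, and 8.2%, 19.9% and 24.1% at m = 32. Other runs of the largest setting lay between 21% and 26%.

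**Shared drift, no parent-by-wave variance.** Let both variables rise by 0.2 total SD, linearly over 0, 6, 12 and 24 months. The scaled times 0, 0.25, 0.5 and 1 have variance 0.137, so the drift covariance is 0.04 × 0.137 = 0.0055 and the bias in β1 is about 0.0055/0.6055 = 0.0090. The standard error is √[0.7/(200 × 4m × 0.6)] = 0.0095 at m = 16 and 0.0068 at m = 32. Rejection is then about 16% and 27% (simulated 16.5% and 27.2%, 1000 runs). A milder version, 0.2 within-parent SD in equal steps with m = 32, gave 14.2%. Drift of 0.1 total SD gave about 6%.

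**Which term repairs what.** A period factor alone leaves parent-specific change untouched (16.8% against 16.7% at 0.2/0.2) but repairs shared drift (5.6% against 14.2%). Estimating within parent and period gave 3.7-6.6% over all the m = 32 settings above, which is nominal within simulation error. Single-period M2 gave 3.7-5.7%.

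**The case against.** The strongest reply is that the combined model has no printed equation. A reader might infer that it definitely lacks a period or parent-by-period term. The article does not say so: M2 is shown with parent and prompt subscripts only, M1 is described as being expanded for multi-period data, and a condensed article may leave the multi-period random effects to the full plan. That stands, so the point is conditional on M2 being carried over as printed. It remains worth making because the only form on the page is the one that fails when pooled.

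A reader might also infer that false positives exceed 5% as a fact. The documents do not support that. The rate is exactly 5% if either variable has no between-wave variance and no drift, and no variance shares are given. Hypothesis 2 and the endurance measure concern practices only; nothing says that a parent's stress or mood level shifts between waves. That half of the mechanism is an assumption.

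The reach is also limited. The period-specific models are planned for every domain and are sound on this point. The stated momentary power rests on 6400 records, so it does not depend on pooling. The study has no formal primary endpoint. Usable event records with a preceding signal may be fewer than 32 per wave, which favours the lower figures.

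Finally, centring the predictor narrows what β1 means. That is fair, and it is why the wave-level part should be kept as its own coefficient and not discarded.

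**Conclusion.** The concern holds conditionally and is confined to the combined fits. M2 as printed, applied unchanged to pooled waves, gives a test of β1 that can exceed the stated 5%. It does so only when practice and predictor both shift by parent and wave, or both drift over two years.

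- Small between-wave shares: about 5-7%.
- Assumed shares of 5-15% (practice) and 10-20% (predictor) of total variance: roughly 7-21%, with the formula reaching 25% at the largest shares and 32 records per wave.
- Assumed shared drift of 0.2 SD in both, with no period term: roughly 14-29% over the spacings and record counts tried.

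All of these rest on 200 parents, four waves, 16 or 32 records per wave and variance shares that the article does not report. Data collection is expected to run to November 2026, so the form can still be settled before all waves are pooled.

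**What to change.** State the form of the combined M2 models:

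1. Add period (T1-T4) as a fixed factor.
2. Add a parent-by-period random intercept nested within the parent effect.
3. Split each momentary predictor into its parent-by-period mean and the deviation from that mean. Enter both, and read the momentary effect from the deviation.

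Pooling the four period-specific within-parent estimates is an acceptable alternative. A period factor alone is not enough.

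The cost is analysis-plan wording, two model terms and a centring step, with no change to data collection. The apparent gain in precision from pooling will be somewhat smaller, and the wave-level association will appear as a separate coefficient that needs its own interpretation.
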